### The Barthel index

The Barthel index [15] is a widely used measure of functional disability. The index was developed for use in the rehabilitation of patients with stroke. This index measures the extent to which someone can function independently and has the mobility necessary for their daily life activities. We will use the BI to establish the relationship between motor recovery (FMMS) and functional recovery.

### The hospital anxiety and depression scale

The hospital anxiety and depression scale (HAD) [16] is a scale widely used to evaluate anxiety and depression in hospitalized patients and has been validated in Spanish [17]. It consists of 14 items: the odd items represent the anxiety subscale and the even items the depression subscale, and both are scored between 0 and 3. The total score is obtained by the summation of all items in each subscale. The severity of the condition increases with the score. In a validation study by Abent *et al*. [18], the use of the HAD scale resulted in a sensitivity of no less than 91.7 (specificity: 65.3) using the optimum threshold score of 11. The authors concluded that although there were no substantial differences in the performances of the four depression rating scales that they studied, the HAD scale was preferred in screening for post-stroke depression because it requires the least amount of time to administer. Thus, we will use the HAD to rule out depression in the patients enrolling and participating in this study.

### Compliance

All subjects will be asked to return the remaining tablets at their next visit. The rate of compliance (percentage) will be calculated on the basis of the returned tablets.

Compliance (%) = 100 - returned tablets/expected intake × 100.

Investigational drugs will be distributed in packs of 50 at each visit.

50 = 1 times/day × 7 days/week × 6 weeks/visit + 8 extras.

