**Methods/design:**

Our study is a randomized, double-blind, placebo-controlled, multicenter clinical trial. We will recruit 86 patients with intracerebral hemorrhage of both sexes, aged >18 years, from four Mexican hospitals. The patients will receive either 20 mg of fluoxetine or a placebo once daily for 90 days. The primary outcome is the mean change in the Fugl-Meyer Motor Scale score between inclusion (day 0) and day 90. The secondary outcomes will be changes in the Barthel Index, the Modified Rankin scale and the National Institutes of Health stroke scale. The outcomes will be measured at day 42 ± 7days and at day 90, for a total of four visits with each subject (at screening and at 0, 42 and 90 days).

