4.1.  Hospital anxiety and depression scale (HAD) score ≥11 points

4.2.  Taking antidepressant drugs two weeks before inclusion

5. Taking neuroleptic drugs or benzodiazepines 2 weeks before inclusion

6. Other major diseases with life expectancy ≤ 3 months.

Withdrawal Criteria

1. Detection of eligibility violations

2. Poor compliance (<90%) or noncompliance

3. Use of any medication or treatment during the trial that could affect the study results

4. Occurrence of a serious adverse event

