4.1. Subject has an acute reaction (allergy, shock) to the investigational product

4.2. Subject develops depression, evidenced by HAD score ≥11 points at Visit 2

5. Subject withdraws consent or is uncooperative

The patients withdrawn after randomization will be followed for outcomes

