3. NIHSS

### Statistical analysis

#### Efficacy assessment

The primary and secondary outcomes will be analyzed using the intention to treat (ITT) method. The full analysis set for the ITT method will include all randomized subjects, regardless of their subsequent withdrawal after enrollment. Continuous variables will be reported as the means ± SD, and categorical variables will be reported as percentages. The Kolmogorov-Smirnoff test will be used to test normality for the continuous variables, and baseline characteristics will be compared by either Student’s *t*-test/U Mann-Whitney for continuous variables or the χ^2^ test (Fisher’s exact test when the expected value is <5) for categorical data.

The primary analysis for efficacy (full-analysis set) will consist of a comparison of the change in FMMS scores at 90 days. To handle the missing data derived from withdrawal and lost to follow-up patients, the last available outcome measure value obtained from the withdrawn/lost to follow-up patient will be used for the analysis (last observation carried forward (LOCF) strategy). A multiple linear regression analysis will be performed to control for baseline factors that show an imbalance.

For the within-group analyses, primary and secondary outcome variables will be evaluated by a paired t-test. Alternatively, for non-normally distributed data, a Wilcoxon test will be performed. Analysis of covariance will be used to analyze differences in each group, adjusting for age and NIHSS as covariates. Statistical significance will be defined as P < 0.05. SPSS for Windows version 17.0 software (SPSS, Inc, Chicago, IL, USA) will be used for the analyses.

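### The compliance formula counts the 8 spare tablets as missed doses, so a fully adherent patient scores 81% at the planned day-42 visit, below the 90% withdrawal limit

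*Protocol article*

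**What the plan says.** The Compliance section of the protocol article sets out the whole rule. Leftovers come back to the site: "All subjects will be asked to return the remaining tablets at their next visit". The score then rests on that count alone, by the formula "Compliance (%) = 100 - returned tablets/expected intake × 100". Each pack contains 50 tablets, broken down as "1 times/day × 7 days/week × 6 weeks/visit + 8 extras", and a pack is given out at each visit.

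The score is tied to an action. The Withdrawal Criteria, under Eligibility criteria, include "Poor compliance (<90%) or noncompliance". Table 1 schedules a pill count at Visits 2 and 3. The Abstract gives the timing: "The outcomes will be measured at day 42 ± 7days and at day 90". The Interventions section prescribes one tablet a day for 90 days.

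Two other statements bear on the consequences. The Withdrawal Criteria end with "The patients withdrawn after randomization will be followed for outcomes". The Efficacy assessment section analyses all randomized subjects by intention to treat and says that, where data are missing, "the last available outcome measure value obtained from the withdrawn/lost to follow-up patient will be used for the analysis".

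**The concern.** A compliance measure should give 100% when every dose is taken and 0% when none is. This one treats every tablet handed back as a dose not taken, although the pack deliberately holds more tablets than the doses due. The spares are named in the pack breakdown but appear nowhere in the formula.

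Because the score feeds a withdrawal criterion, the slip matters beyond reporting. If sites apply the rule as printed at Visit 2, patients who have done exactly what was asked are taken off study drug about halfway through treatment. Stopping fluoxetine early in its own arm reduces the exposure contrast with placebo and so shrinks any true difference in the day-90 change in the Fugl-Meyer Motor Scale (FMMS). If sites correct for the spares on their own initiative, these withdrawals are avoided, but the criterion is then applied by a rule the protocol article does not state.

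**Working it through.** **Inputs, all from the protocol article.** Pack of 50 tablets, 42 expected doses and 8 spares (Compliance); one tablet a day for 90 days (Interventions); Visit 2 on day 42 ± 7, that is days 35 to 49 (Abstract); withdrawal limit below 90% (Withdrawal Criteria).

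**Pack size reproduced.** 1 × 7 × 6 + 8 = 50, as stated.

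**Model.** The first pack is issued on day 0, and a fully adherent patient has taken d tablets by a Visit 2 on day d. Tablets returned = 50 - d. Printed score = 100 - (50 - d)/E × 100, where E is expected intake. The text does not define E, so three readings are shown: days elapsed (E = d), the six-week figure (E = 42), and everything supplied (E = 50).

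| Visit 2 on day | Returned | E = d | E = 42 | E = 50 |
|---|---|---|---|---|
| 35 | 15 | 57.1% | 64.3% | 70.0% |
| 42 | 8 | 81.0% | 81.0% | 84.0% |
| 45 | 5 | 88.9% | 88.1% | 90.0% |
| 46 | 4 | 91.3% | 90.5% | 92.0% |
| 49 | 1 | 98.0% | 97.6% | 98.0% |

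The fully adherent patient is below 90% on days 35 to 45, which is 11 of the 15 permitted days, with E = d or E = 42. With E = 50 it is days 35 to 44, since day 45 gives exactly 90.0%. The planned day fails on all three readings.

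**Sensitivity to the dose count.** If 41 tablets have been taken at the day-42 visit, 9 are returned: 100 - 9/41 × 100 = 78.0%. If 43 have been taken, 7 are returned: 100 - 7/43 × 100 = 83.7%. The conclusion does not hang on whether the day-0 or visit-day dose is counted.

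**What passing requires at day 42 (E = 42).** Returned ≤ 0.10 × 42 = 4.2, so at most 4 tablets. Then 50 - 4 = 46 tablets must be gone for 42 prescribed doses, 4 more than the patient should have used.

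**The whole scale is shifted.** With m missed doses at day 42 the patient returns 8 + m, so the printed score is 100 - (8 + m)/42 × 100. The true figure is (42 - m)/42 × 100. The gap is always 8/42 × 100 = 19.0 points:

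- m = 0: printed 81.0%, true 100%.
- m = 4: printed 71.4%, true 90.5%.
- m = 42: printed -19.0%, true 0%.

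**Doses forgone.** Withdrawal at day 42 leaves 90 - 42 = 48 of the 90 doses untaken.

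**The case against.** The strongest defence is evident intent. The 8 tablets are labelled as spares right beside the formula, and a score of 81% for perfect intake, or below zero for none, would be noticed at the first pill counts. The article also condenses a fuller protocol, whose pill-count instructions may deduct the spares. This lowers the chance of harm, but it does not repair the text: the formula is stated in full, no sentence deducts the spares, and it governs a withdrawal decision. Nor would deducting a fixed 8 be enough away from day 42. At day 35 an adherent patient returns 15, and 100 - (15 - 8)/35 × 100 = 80.0% (83.3% with a denominator of 42).

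The defence is right that the effect on the result is bounded. The intention-to-treat set does not change, the error is the same in both arms, withdrawn patients are to be followed, and the article gives compliance no role in any analysis. A day-42 FMMS value would be carried forward to day 90 only if that promised follow-up also failed.

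Three stronger readings may tempt a reader, and the documents do not support them.

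- That no permitted Visit 2 date is safe. A fully adherent patient seen on days 46 to 49 passes at Visit 2 on every reading of expected intake. Low scores at Visit 3 do not fill the gap, because treatment ends at day 90 and a score there cannot take anyone off drug.
- That every compliance rate from the formula is too low. If leftovers are not re-issued and Visit 2 falls on day 40 or earlier, the second pack of 50 must cover 50 or more days. Nothing is returned and the Visit 3 score is 100%, which is correct at day 40 and too high before it, when tablets run out. Lost tablets also raise the score.
- That the four sites would in fact apply the rule differently. This is possible, but nothing in the article shows it.

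**Conclusion.** The point holds for Visit 2. As written, the formula gives a patient with no missed dose 81.0% on the planned day (84.0% with a denominator of 50), and below 90% on days 35 to 45 of the day 35 to 49 window (days 35 to 44 with a denominator of 50). That patient meets the withdrawal criterion.

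This rests on one tablet a day from a pack issued on day 0, all leftovers returned, and the printed formula applied without deducting the spares. Under literal use, adherent patients in both arms would stop study drug with about 48 of 90 doses left, and any true effect would be diluted. How much cannot be calculated from the article, since it depends on how many sites apply the rule literally and on how benefit relates to length of treatment.

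The sample size, the randomization and the analysis set are untouched. The formula should be corrected because it drives a treatment decision, but it does not threaten the validity of the planned comparison by itself.

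**What to change.** Replace the formula with:

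Compliance (%) = (tablets dispensed + any carried over - tablets returned) / doses due since the last dispensing × 100,

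and apply the 90% limit to that figure. At a day-42 visit:

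- 8 returned: (50 - 8)/42 = 100%.
- 12 returned: (50 - 12)/42 = 38/42 = 90.5%, stays in.
- 13 returned: (50 - 13)/42 = 37/42 = 88.1%, flagged.

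Because the denominator is doses due, the formula works on any day of the Visit 2 window. State whether leftover tablets are re-issued at Visit 2, so that the carried-over term is known.

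The cost is one changed line in the protocol and the matching field in the case report file, using the pill counts already scheduled at Visits 2 and 3. It needs no extra patients, visits, tablets or unblinding, and it can be made although recruitment has begun; scores already calculated can be redone from the recorded counts. Lost tablets would still count as taken, as they do now.

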### Outcomes

Both primary and secondary end points will be measured at each visit according to the study schedule (Table 1).

### Primary outcome

The primary outcome is the mean change in FMMS score between inclusion (day 0) and day 90.

### Secondary outcomes

Both within-group and between-group analyses will be performed for each outcome. The differences in the following variables between the baseline (visit 1) and the last visit (visit 3) will be calculated.

1. Barthel Index

2. Modified Rankin scale

3. NIHSS

### Statistical analysis

#### Efficacy assessment

The primary and secondary outcomes will be analyzed using the intention to treat (ITT) method. The full analysis set for the ITT method will include all randomized subjects, regardless of their subsequent withdrawal after enrollment. Continuous variables will be reported as the means ± SD, and categorical variables will be reported as percentages. The Kolmogorov-Smirnoff test will be used to test normality for the continuous variables, and baseline characteristics will be compared by either Student’s *t*-test/U Mann-Whitney for continuous variables or the χ^2^ test (Fisher’s exact test when the expected value is <5) for categorical data.

The primary analysis for efficacy (full-analysis set) will consist of a comparison of the change in FMMS scores at 90 days. To handle the missing data derived from withdrawal and lost to follow-up patients, the last available outcome measure value obtained from the withdrawn/lost to follow-up patient will be used for the analysis (last observation carried forward (LOCF) strategy). A multiple linear regression analysis will be performed to control for baseline factors that show an imbalance.

For the within-group analyses, primary and secondary outcome variables will be evaluated by a paired t-test. Alternatively, for non-normally distributed data, a Wilcoxon test will be performed. Analysis of covariance will be used to analyze differences in each group, adjusting for age and NIHSS as covariates. Statistical significance will be defined as P < 0.05. SPSS for Windows version 17.0 software (SPSS, Inc, Chicago, IL, USA) will be used for the analyses.

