#### Sample size calculation

A sample size of 35 in each group will be sufficient to detect a clinically important difference of 14.5 points on the FMMS, assuming a standard deviation of 21.3 FMMS points on the basis of the findings of the fluoxetine in motor recovery of patients with acute ischaemic stroke (FLAME) trial [12], using a two tailed *t*-test of the difference between means, a power of 80%, and a significance level of 5%. This number has been increased to 44 per group (total of 88), to allow for a predicted 20% loss to follow-up.

The formula for the sample size for comparison of two means (two-sided) is as follows:

$$n=\frac{2\sigma^{2}{\left(Z_{a}+Z_{b}\right)}^{2}}{\delta^{2}}$$

$$Z_{a}=1.96$$

$$Z_{b}=0.84$$

δ = size of difference of clinical importance = 14.5

σ = standard deviation of the primary outcome variable = 21.3

$$n=\frac{2*21.3^{2}{\left(1.96+0.84\right)}^{2}}{14.5^{2}}\approx 35$$

Adjusted for 20% patients lost to follow-up:

$$n_{c}=\frac{n}{1-l}\approx 44$$

*l* = expected frequency of patients lost to follow-up = 0.20

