## Discussion

The degree of recovery and the speed of recovery from disabilities secondary to ICH are different from the recovery of patients with CI, although this difference has rarely been documented [19,20]. This is partly because the evidence comes from countries where there are a disproportionately lower number of patients with ICH compared with CI available to extract adequate conclusions. However, the existing evidence appears to demonstrate that patients with ICH recover faster and to a quantitatively greater degree compared with patients with CI. For example, in the study by Katrak et al. [21], even though the studied patients with ICH had a greater level of disability at discharge, they achieved significantly greater gains in function than patients with CI after rehabilitation. This was the case regardless of the severity of disability on admission.

The study by Nannetti et al. [22], in which 20% of the studied stroke patients suffered from ICH, patients receiving antidepressants (mostly SSRIs) made the most rapid recoveries during the hospital stay period. However, lower levels of improvement were seen after discharge, which the authors attribute to the fact that the antidepressant treatment was not continued after discharge by some patients (20.4%). This recovery was observed in the group of patients with post stroke depression (PSD) as well as in those without PSD.

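### LOCF is the only stated missing-data rule for the primary FMMS change: it does not say that day-90 values observed after withdrawal are used, and it freezes recovery for values truly missing

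*Protocol article*

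**What the plan says.** The Efficacy assessment section of the protocol article analyses all randomized patients. For data missing through withdrawal or loss to follow-up it gives one rule: "the last available outcome measure value obtained from the withdrawn/lost to follow-up patient will be used for the analysis". No other handling of missing data is stated for the primary outcome, the change in FMMS from day 0 to day 90.

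The Withdrawal Criteria end with the statement that "The patients withdrawn after randomization will be followed for outcomes". The grounds for withdrawal include "Subject develops depression, evidenced by HAD score ≥11 points at Visit 2", compliance below 90% and serious adverse events.

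Table 1 schedules the FMMS at screening, Visit 2 (day 42) and Visit 3 (day 90) only.

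The Sample size calculation plans for a "clinically important difference of 14.5 points on the FMMS", "assuming a standard deviation of 21.3 FMMS points", and then adds patients for attrition: "This number has been increased to 44 per group (total of 88), to allow for a predicted 20% loss to follow-up".

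**The concern.** There are two linked problems.

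First, one section treats withdrawal as producing missing data, while another promises outcome data on withdrawn patients. The analysis text does not say what happens to a day-90 FMMS measured after withdrawal. Two analysts could compute different primary results from the same data.

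Second, the endpoint is recovery. With the FMMS measured only three times, a carried value is either the baseline score (a change of zero) or the day-42 score. Either one assumes that recovery stopped there. If loss is equal between arms, a true effect is diluted. If loss is unequal, a difference can appear with no motor effect behind it. Unequal loss is plausible here, because a depression score at Visit 2 triggers withdrawal and the test drug is an antidepressant.

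**Working it through.** **Inputs from the protocol article:** difference 14.5, SD 21.3, two-sided 5% level, 80% power, 35 per group raised to 44 for 20% loss.

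**Assumptions, not in the documents:** the fraction f of the 90-day change already reached at the carried visit, the mean 90-day change, the withdrawal proportions by arm, and that the whole predicted 20% is carried forward.

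**Plan's own figure.** 2 × 21.3² × (1.96 + 0.84)² / 14.5² = 33.8, so 34 by the printed formula. The exact t-test gives 79.0% power at 34 and 80.2% at 35, so 35 is right for the t-test. Then 35 / 0.80 = 43.75, so 44. The figures reproduce. Dividing by 1 − 0.20 assumes that lost patients leave the analysis. The analysis section instead keeps them in, with carried values.

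**Dilution with equal 20% loss.** Expected LOCF difference = 14.5 × (0.8 + 0.2f). Standard error with 44 per arm = 21.3 × √(2/44) = 4.54. Power by the normal approximation = Φ(difference / 4.54 − 1.96).

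| f | Expected difference | Power |
|---|---|---|
| 0 (all carry baseline) | 11.60 | 72% |
| 0.25 | 12.33 | 77.5% |
| 0.5 | 13.05 | 82% |
| 0.6 | 13.34 | 84% |
| 0.75 | 13.78 | 86% |
| 1 (nothing lost) | 14.50 | 89% |

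Break-even for 80%: the difference must be at least (1.96 + 0.84) × 4.54 = 12.7. So 0.8 + 0.2f = 12.7 / 14.5 = 0.877, and f is about 0.39.

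The table holds the SD at 21.3. If the variance is instead that of a mixture of completers and carried patients, power at f = 0 is 76%, 69% or 61% for assumed placebo changes of 10, 20 or 30 points. At f = 0.5 it is 83% to 87%.

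**Bias with unequal loss and no true effect.** False difference = (placebo loss − fluoxetine loss) × (1 − f) × mean change. Type I error is approximately Φ(bias / 4.54 − 1.96) + Φ(−bias / 4.54 − 1.96).

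- Low end: 0.10 × 0.30 × 25 = 0.75 points, type I error about 5%.
- Middle (30% v 10%, f = 0.6): 0.20 × 0.40 × 25 = 2.0 points, about 7%. This is 2.0 / 14.5 = 14% of the planned difference.
- High end: 0.20 × 0.50 × 35 = 3.5 points, about 12%.

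With equal loss the bias under no effect is zero. If the larger loss is on fluoxetine, the sign reverses.

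**The case against.** **The text does not say that observed values are overwritten.** A reader might infer that the plan discards day-90 scores from withdrawn patients. The documents do not support that. If a withdrawn patient attends day 90 as the Withdrawal Criteria foresee, that score can be read as the last one available, and LOCF then touches only values never obtained. On that reading most of the bias from depression-related withdrawal disappears. This stands. What remains is that the analysis section does not say so, and that LOCF still governs those actually lost.

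**Power need not fall short.** A reader might infer that the stated 80% is not met. It is met once about 39% of the change has been reached at the carried visit. Patients withdrawn on their Visit 2 depression score have an FMMS scheduled at that same visit. A shortfall needs substantial loss before Visit 2, and the documents give no figure for that. The bias and power problems also tend to belong to different scenarios. With 30% v 10% withdrawn, f = 0.6, a placebo change of 25 and a true 14.5 effect, the LOCF difference is 39.5 × 0.96 − 25 × 0.88 = 15.9, which is larger than planned.

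**Direction and size are assumed.** Serious adverse events and poor compliance also trigger withdrawal and could offset or reverse an excess on placebo. The Discussion says that "patients with ICH recover faster and to a quantitatively greater degree compared with patients with CI", but this compares two stroke types. It does not show improvement continuing up to day 90, and faster recovery would leave less for LOCF to lose after day 42. These points stand.

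**An article may leave detail to a statistical analysis plan.** True of detail, but here the article itself fixes the rule.

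**Conclusion.** The point holds in a limited form. LOCF is the sole stated rule for missing primary data and suits a recovery endpoint poorly. Its wording has to be reconciled with the commitment to follow withdrawn patients.

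Under equal 20% loss, the planned effect shrinks to between 11.6 points (all carry baseline) and 13.05 (half the change reached). Under assumed withdrawal gaps of 10 to 20 percentage points, day-42 fractions of 0.5 to 0.7 and mean changes of 25 to 35 points, the bias is about 0.75 to 3.5 points and type I error about 5% to 12%. At the low end that inflation is negligible. The bias favours fluoxetine only if more placebo patients are lost, so actual size and direction are unknown.

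No general failure of the sample size follows. Power is about 72% at SD 21.3 only in the extreme case where all 20% carry baseline.

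**What to change.** 1. State in the Efficacy assessment section that the observed day-90 FMMS is used for every randomized patient who has one, including those withdrawn, and align this with the Withdrawal Criteria. If all day-90 values were observed and the full effect kept, power at 44 per arm would be 88% to 89%.
2. For values still missing, replace LOCF as the primary method by one of two options:
   - a mixed model for repeated measures on the FMMS at days 42 and 90, with arm × visit, baseline FMMS × visit and site; or
   - multiple imputation by arm using baseline FMMS, day-42 FMMS and the Visit 2 HAD score. This option brings in the depression score that triggers withdrawal.
3. Keep LOCF as a sensitivity analysis only.

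The change should be fixed before unblinding. It costs some wording and a little more analysis work. Standard software fits either method, and no new data are needed, since Table 1 already schedules the FMMS and the depression scale at the relevant visits.

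### The efficacy regression takes its covariates from observed baseline imbalance, and the plan neither names the primary between-arm model nor ranks the regression and the ANCOVA beside it

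*Protocol article*

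**What the plan says.** All of this is in the Protocol article, mainly in Efficacy assessment.

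- **Primary analysis.** It compares 90-day FMMS change in the full analysis set. No test or model is named there. A two-tailed t-test appears only under Sample size calculation.
- **Regression.** In the same paragraph: "A multiple linear regression analysis will be performed to control for baseline factors that show an imbalance". The preceding paragraph plans significance tests of baseline characteristics between arms. Neither a threshold for imbalance nor a list of candidate factors is given.
- **ANCOVA.** The next paragraph adds an analysis of covariance with age and NIHSS. Its wording speaks of differences in each group and it stands among the within-group methods, so it is unclear whether it compares the arms.
- **Within-group tests.** Secondary outcomes states: "Both within-group and between-group analyses will be performed for each outcome". Efficacy assessment adds: "For the within-group analyses, primary and secondary outcome variables will be evaluated by a paired t-test", with Wilcoxon for non-normal data.
- **Threshold.** One rule covers every test: "Statistical significance will be defined as P < 0.05".

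Baseline FMMS and site are not named as covariates anywhere.

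**The concern.** A baseline difference between randomised arms is a chance event. Its P value carries no information on whether the factor predicts FMMS change, and that is what decides whether adjusting for it helps. A rule driven by imbalance therefore lets the accident of allocation choose the model. It can admit a factor with no bearing on motor recovery, and it will usually leave out baseline FMMS, although the outcome is change from that value.

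The ranks also matter. A reader of the final report could meet an unadjusted comparison, a regression with data-chosen covariates and an ANCOVA, all judged at the same threshold. The plan does not say which decides the trial if they disagree.

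The within-group tests add a further risk. Patients are expected to recover without the drug, and the Discussion section itself expects substantial recovery after intracerebral haemorrhage. A significant change in the fluoxetine arm would be easy to report as efficacy.

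**Working it through.** **1. The plan's own figure.** Inputs from Sample size calculation: difference 14.5, SD 21.3, z-values 1.96 and 0.84.

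- Printed formula: 2 × 21.3² × (1.96 + 0.84)² / 14.5² = 33.84.
- The exact two-sample t-test calculation gives 34.86, so 35 per arm, as stated.
- With 20% loss: 35 / 0.80 = 43.75, so 44 per arm and 88 in total.

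The planned size stands and is not affected by this point.

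**2. How often chance changes the regression.** Assume that imbalance means P < 0.05; the plan does not say so.

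- Any given factor, baseline FMMS included, is then selected in 5% of trials and left out in 95%, however prognostic it is.
- With 8 independent factors (an assumed number), the chance that at least one is selected is 1 − 0.95⁸ = 34%, about one trial in three.

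**3. False-positive rate by analysis.** Simulated with no treatment effect: 4,000 trials per scenario, 35 or 44 per arm, 8 independent baseline factors, normal or skewed outcome. Assumed correlations with FMMS change were 0 to −0.3 for age, 0 to −0.6 for NIHSS and 0 to 0.25 for a third factor. The ANCOVA is read as a comparison between arms. Simulation error is about ±0.7 percentage points.

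| Route | False-positive rate |
|---|---|
| Unadjusted t-test alone | 3.9% to 5.6% |
| ANCOVA with age and NIHSS alone | 4.3% to 5.7% |
| Imbalance-selected regression alone | 2.8% to 4.9% |
| Success if any of the three is significant | 5.1% to 8.6% |

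A separate repeat with normal outcomes gave 5.7% to 9.0% for the last row. Three independent tests would give 1 − 0.95³ = 14%. The figure here is lower because the three analyses share the same data.

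**4. Within-group tests.** Inputs: SD of change 21.3 (Sample size calculation) and the same true mean recovery m in both arms (assumed). The power p of the paired t-test comes from the noncentral t distribution with noncentrality m√n / 21.3. The chance that fluoxetine is significant and placebo is not is p(1 − p).

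| m (points) | p, n = 44 | Fluoxetine only, n = 44 | Fluoxetine only, n = 35 |
|---|---|---|---|
| 5 | 0.331 | 0.331 × 0.669 = 22% | 20% |
| 7 | 0.568 | 0.568 × 0.432 = 25% | 25% |
| 10 | 0.861 | 0.861 × 0.139 = 12% | 18% |

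At 15 points or more both arms are significant in at least 96% of trials (p² = 0.963 at 35 per arm and 0.991 at 44). So at modest recovery the contrast misleads, and at large recovery it says nothing about the drug.

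**5. One fixed model.** A single prespecified ANCOVA has a simulated error of 4.3% to 5.7%, which is 5% within simulation error. Its power at 35 per arm (normal approximation) is about 81% if the covariates explain nothing, 85% at an assumed multiple correlation of 0.3, and 91% at 0.5.

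**The case against.** The strongest reply is that the plan does have a primary analysis. Only one comparison carries that label, the Hypothesis section is framed between arms, and the sample size is based on a two-tailed t-test. Read together, these point to an unadjusted t-test. Detailed covariate lists and the ranking of supportive analyses are often left to an analysis plan, and this is a condensed article. The ANCOVA also fixes two plausible covariates whatever the imbalance.

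Much of that stands, and it rules out several stronger readings that a reader might infer:

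- **That the plan fails to hold 5%.** It does not follow. No single route exceeds 5% beyond simulation error, and the imbalance-selected regression tends to be conservative. The excess needs a free choice among three analyses, which the document does not authorise.
- **That normality testing decides the primary model.** The plan says "The Kolmogorov-Smirnoff test will be used to test normality for the continuous variables", but it ties the resulting choice of test to baseline comparisons and within-group tests, not to the comparison between arms.
- **That some imbalance is nearly certain because Table 1 lists so many items.** Treating about 37 items as independent and all tested at 5% gives 1 − 0.95³⁷ = 85%. But many overlap (haemoglobin with haematocrit, the lipid fractions, INR with prothrombin time), and the plan does not say that all will be tested.
- **That within-group results are offered as proof of efficacy.** They are not; the risk is one of misreading.

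The reply does not remove the selection rule itself. It is stated text, placed directly after the primary analysis and missing baseline FMMS. A later analysis plan would have to overturn it, not merely fill it in.

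**Conclusion.** The point holds as a defect of specification. Covariates for the efficacy regression are chosen from observed imbalance with no criterion, baseline FMMS is in no fixed set, the primary model is unnamed, and the regression and the ambiguously worded ANCOVA have no stated rank.

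The effect on error is conditional and moderate: about 5% or less for each route alone, and roughly 5% to 9% only if any of the three may be quoted. That range rests on the assumed covariate strengths, on 8 independent factors and on a 5% criterion for imbalance. The within-group figure of 12% to 25% rests on SD 21.3, 44 per arm and assumed mean recoveries of 5 to 10 points. It measures how often a misreading could arise, not the error rate of the planned comparison.

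This should be changed, but it does not invalidate the design or the sample size.

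**What to change.** Before unblinding:

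1. Name one ANCOVA comparing FMMS change at day 90 between arms as the sole confirmatory test at two-sided 5%. Prespecify baseline FMMS, age, baseline NIHSS and site as covariates. Site belongs there because the randomised supply is allotted by site, 22 participants each. Specify the baseline NIHSS value, since NIHSS is also measured after treatment starts.
2. Delete the imbalance trigger. Label the unadjusted t-test, a rank-based test and any imbalance-adjusted model as sensitivity analyses.
3. Reword the ANCOVA sentence so that it clearly compares the arms.
4. Report within-group changes descriptively, with confidence intervals and without P values.

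The cost is wording and a few degrees of freedom: three for baseline FMMS, age and NIHSS, plus three for four sites, so 6 of the 70 − 2 = 68 available with 35 evaluable per arm. Adjustment for an unexpected imbalance remains possible, but only as a sensitivity analysis. The sample size need not rise.
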